## Abstract

Disturbed sleep is common in adolescents. Ingested nutrients help regulate the internal clock and influence sleep quality. The purpose of this clinical trial is to assess the effect of protein tryptophan (Trp)/large neutral amino acids (LNAAs) ratio on sleep and circadian rhythm. Ingested Trp is involved in the regulation of the sleep/wake cycle and improvement of sleep quality. Since Trp transport through the blood–brain barrier is competing with LNAAs, protein with higher Trp/LNAAs were expected to increase sleep efficiency. This randomized double-blind controlled trial will enroll two samples of male adolescents predisposed to sleep disturbances: elite rugby players (n = 24) and youths with obesity (n = 24). They will take part randomly in three sessions each held over a week. They will undergo a washout period, when dietary intake will be calibrated (three days), followed by an intervention period (three days), when their diet will be supplemented with three proteins with different Trp/LNAAs ratios. Physical, cognitive, dietary intake, appetite, and sleepiness evaluations will be made on the last day of each session. The primary outcome is sleep efficiency measured through in-home electroencephalogram recordings. Secondary outcomes include sleep staging, circadian phase, and sleep-, food intake-, metabolism-, and inflammation-related biochemical markers. A fuller understanding of the effect of protein Trp/LNAAs ratio on sleep could help in developing nutritional strategies addressing sleep disturbances.

## 1. Introduction

Adolescents are vulnerable to poor sleep [1,2]. A high social rhythm disruption, favorable during adolescence, would be associated to a substantial desynchronization in one’s routine that would likely leads to erratic sleep–wake pattern or promote sleep disruption among this population [3]. Obesity and elite sport are two factors that have been separately associated with sleep disturbances. They have a negative impact on holistic development, with lowered performance, both physical (recovery, metabolism, growth, and weight control) and cognitive (learning, memory, decision-making, and vigilance). Several studies show that obesity is associated with decreased sleep efficiency and increased arousal [4,5]. This impairs energy balance control by increasing energy intake through a modified sense of satiety and hunger [6]. In parallel, recent studies report that sleep disturbances are widespread in young athletes especially those practicing contact sports such as rugby [7,8]. Poor sleep impairs their athletic performances [9] and substantially increases the risk of injury, burnout, and concussion [10,11].

Besides endogenous factors linked to maturational changes during adolescence which push for a delay in the timing of sleep and increase the risk of sleep disturbances [1]. Other external factors specific for each population (obese or athlete) exacerbate poor sleep outcomes. In adolescents with obesity, the involvement of a complex interaction among sleep, obesity, metabolic disruption, and low grade inflammation was advanced [12,13]. On the other hand, the increased time demands by elite sports pressures including high training demands, evening intense exercise, competition, travel, and strict schedules contribute to excessive stress, anxiety, physiological excitement (e.g., increased heart rate at bedtime), pain, and muscle soreness which impair sleep in young athletes [7,14].

To date, few non-pharmacological approaches have been implemented to address sleep disturbances in these populations. A wide range of papers emphasize that external Zeitgeber such as nutrients and physical activity play a part in regulating the internal clock and determining sleep quality [15,16]. Nutrients reprogram peripheral clocks such as the liver or the gut clock by exerting an effect on the transcriptional and translational regulation of molecular clocks (e.g., CLOCK/BMAL) which generates a considerable reorganization of homeostasis and specific metabolic pathways [17]. Moreover, we have recently noted a growing interest in the effect of dietary intake on sleep and several reviews have been published over the last decade [18,19,20,21,22]

One of the macronutrients whose effect on sleep remains controversial is protein. Some amino acids, besides their use as substrates for protein synthesis, also act as precursors for the biosynthesis of compounds involved in various physiological processes. Experimentally, the availability of amino acid precursors can influence the rate of neurotransmitter biosynthesis [23,24,25,26]. However, the functional consequences of the intake of amino acid precursors on the nervous system are still imperfectly known. One study reported that ingested tryptophan (Trp) is involved in the regulation of the sleep–wake cycle and the improvement of sleep duration and quality [27]. Others have found that high protein intake, especially in the evening, is associated with increased alertness. This has been explained by the stimulating effect of certain amino acids on excitatory hormones such as adrenaline and noradrenaline [28,29,30]. Although it is hard to draw definite conclusions, it has also been suggested that Trp transport through the blood–brain barrier (BBB) competes with large neutral amino acids (LNAAs). This could explain why high protein intake decreases Trp bioavailability in the brain and increases alertness [31]. Previous studies on tryptophan depletion have shown that decreasing circulating tryptophan impairs sleep (e.g., increased arousal and delayed REM sleep) [32,33]. Moreover, it was suggested that small amount of dietary Trp intake could improve sleep efficiency in insomniac subjects [34]. The pilot study by Ong et al. (2017) also reported favorable effect of Trp rich protein on accelerometry measured sleep among young adults without sleep complaints [35].

Recent reviews strongly recommended nutrition as a basic option to improve sleep, especially among the population with sleep disturbances [36,37]. A more comprehensive understanding of the relationship between dietary protein (Trp/LNAAs ratio) and sleep could help in developing nutritional strategies to address adverse effects on adolescent sleep, especially among vulnerable persons such as adolescents with obesity or junior elite athletes. Here, we describe the design of the PROTMORPHEUS study and highlight the importance of carrying out this trial under free-living ecological conditions.

## 2. Materials and Methods

### 2.1. Study Participants, Eligibility Criteria and Recruitment Procedure

Adolescents will be recruited and evaluated throughout the study at three sites: The Department of Pediatrics, University Hospital, Clermont-Ferrand, France; the Montferrand Sports Association—Rugby Section, Clermont-Ferrand, France; and the Pediatric Obesity Center (Tza Nou, La Bourboule, France). Male adolescents aged 14–17 years over Tanner Stage 3 will be enrolled in this study who are rugby players engaged in the under 17 years national category or with obesity (BMI) ≥ 95th percentile. A total of 48 adolescents (24 rugby players and 24 with obesity) will be recruited. Eligibility criteria are presented in Table 1. A physician will assess eligibility in the Department of Pediatrics, University Hospital, Clermont-Ferrand, France. All diagnosed sleep disorders will be considered as exclusion criteria and all recruited adolescents will be screened for Obstructive Sleep Apnea using the Berlin questionnaire [38]. Participants will also be screened for depression using the Kutcher Adolescent Depression Scale (KADS) where the score ≥ 6 will be considered as exclusion criteria [39]. Moreover, they will not present any eating disorder according to the Dutch Eating Behavior Questionnaire (DEBQ) [40].

This study will be based at both “Tza Nou” (Obesity Treatment Center for Children and Adolescents) where recruited adolescents with obesity are housed, and the Rugby Training Center of the Montferrand Sports Association for young elite rugby players. The investigators will travel to the sites with the laboratory equipment for ambulatory running of the study. The adolescents will be informed and agree to take part in the study with parental written consent. The experimental design complies with the ethical principles in the 2008 revision of the Declaration of Helsinki and has been approved by an ethics committee (comité de protection des personnes (CPP) Sud Meditérrannée II, registration number: 2018 A23) prior to the study launch (clinical trial No. NCT04041934).

### 2.2. Randomization

Treatments (Trp/LNAAs ratio: PROT-REF = 0.04, PROT1 = 0.07, PROT2 = 0.11) will be assigned by randomization at a ratio of 1:1:1 in each sample. Stratification will be performed every six subjects (one experimental group). Each participant will have a single identification number will identify each participant. The participant number will be assigned chronologically on the randomization list. A comprehensive document describing the randomization procedure will be safeguarded at the Children’s Clinical Research Centre, INSERM CIC 1405. Indistinguishable protein containing different Trp/LNAAs ratio will be sent by Oxsitis (Clermont-Ferrand, France). Investigators, patients, and evaluator will be blinded to the patient’s treatment allocation. A computer program will generate the coding list and will allocate coding numbers to participants from the specific trial site. The data will be collected and recorded on case report forms (CRFs) by local research coordinators blinded to the randomized intervention. A trained research coordinator, also blinded to the randomized intervention, will centralize and record data in an electronic database.

### 2.3. Design Overview

PROTMORPHEUS is a randomized, double-blind, controlled, monocentric trial in which each subject acts as his own control to reduce interindividual variability.

#### 2.3.1. Objectives

The primary objective of this study is to investigate the effect of proteins with different Trp/LNAAs ratios on sleep efficiency (Figure 1). Secondary objectives are to determine the effect of protein Trp/LNAAs ratio on:Other sleep outcomes such as sleep staging, sleep onset latency (SOL) and wake after sleep onset (WASO)Circadian phase measured by DLMOMorning cortisol peakBiochemical markers related to sleep, food intake, metabolism, and inflammationMetabolic fitness measured by indirect calorimetry on submaximal testMuscle fatigue measured by time of maintenance of muscle strengthCognitive performances measured by a battery of tests including Stroop, trail marking, barrage, California verbal learning, and multiple object trackingEnergy intake and proportion of that energy derived from each macronutrient class (carbohydrate, fat, and protein) measured on meals offered ad libitumAppetite sensations (visual analog scales)Sleepiness rate (Karolinska scale)

#### 2.3.2. Experimental Sessions

At baseline, participants will undergo numerous assessments for anthropometry, body composition, and resting metabolic rate (RMR). They will complete the Morningness–Eveningness Questionnaire for Children and Adolescents (MEQ-CA) to determine their chronotype [41], the self-report Pittsburgh sleep quality index (PSQI) to measure subjective sleep quality [42], the Epworth sleepiness scale (ESS) to measure daytime sleepiness [43], and the international physical activity questionnaire (IPAQ-SF) to estimate habitual physical activity level [44].

After the baseline and one week before to the experimental session launch of each group, time in bed (TIB) will be fixed, and sleep–wake cycle will be continuously monitored using accelerometry. Participants will also be equipped with the Sleep Profiler-PSG2 TM (Advanced Brain Monitoring, Carlsbad, CA) to familiarize them with sleeping with the device. Thereafter, three sessions will be conducted. Each session will be held over a week (Figure 2). Given the potential effect of electronic media (smartphone, laptop, etc.) on sleep and circadian rhythm [45], their evening use will be prohibited during the study.

To limit inter-individual differences, participants will undergo a washout period (three days). During this period, their diet will be set to the recommended dietary allowance (RDA) (1.8 × basal metabolism for athletes and 1.3 × basal metabolism for adolescents with obesity) with protein intake fixed at 1.2 g.kg^−1^. The RDA will be calculated individually for each subject. Three meals and a snack will be offered each day. The meal trays will be prepared in advance and will be the same between sessions. At the last night of washout (Night 3), five saliva samples will be collected to capture DLMO (3, 2, and 1 h before bedtime, bedtime, and 1 h after bedtime). Participants will be fitted with the Sleep Profiler-PSG2 TM for the night. On awakening next day, two saliva samples (on awakening and 60 min later) will be taken to measure morning cortisol level, and blood samples will be collected in the fasting state to measure several biochemical markers related to sleep, food intake, metabolism, and inflammation. During the next three days, dietary intake will be supplemented with protein shakes (PROT-REF = 0.04, PROT1 = 0.07, or PROT2 = 0.11). From Day 4 to Day 6, the diet will be iso-energetic to the washout period (Days 1—3) diets. However, protein intake will be raised from 1.2 to 1.6 g.kg^−1^ through (PROT-REF, PROT1, or PROT2) shakes and intake from other macronutrients will be adjusted accordingly. Similar to Night 3, participants will collect five saliva samples and undergo electroencephalogram (EEG) recordings during Night 6.

At Day 7 (Figure 3), on awakening, saliva samples and blood samples will be collected. Food will then be offered ad libitum in four meals (breakfast, lunch, afternoon snack, and dinner) representing 24 h energy intake. Participants will be asked to fill out visual analog scales for their appetite sensations and sleepiness level throughout the day. After breakfast, participants will take part in evaluations including metabolic fitness on submaximal test, muscle fatigue measured by time of maintenance of strength of the knee extensor muscles, and cognitive performance measured by a battery of tests (Stroop, trail marking, trail-making task, barrage test, California verbal learning, and multiple object tracking).

Protein intakes during the first three days of each experimental session will be 1.2 and 1.6 g.kg^−1^ the following three days. The average nutritional requirement (RDA) for tryptophan is 4 mg.kg^−1^.day^−1^. The French food safety agency’s opinion on the use of tryptophan in dietary supplement indicates a threshold of 200 mg.day^−1^. The protein supplementation used in this study will not exceed this tryptophan threshold.

### 2.4. Measurements

#### 2.4.1. Baseline Assessments

Anthropometric characteristics and body composition

Body mass (BM) will be measured with a digital scale, standing with minimal clothing. Height will be measured barefoot using a stadiometer. Body mass index (BMI = body mass divided by height squared in kg.m^-2^) will then be calculated. Fat mass, visceral fat mass, and fat-free mass will then be established using dual-energy X-ray absorptiometry (DXA) scans (QDR4500Ascanner, Hologic, Waltham, MA, USA).

Resting metabolic rate

Resting metabolic rate (RMR) will be measured in the fasting state, using indirect calorimetry (MetaMax 3b, Cortex Biophysik, Leipzig, Germany). As recommended by the manufacturer, gas analysis will be calibrated before the test. The test will be held in a thermoneutral environment (22–25 °C). Participants will lie in a supine position for 45 min before starting the measurements. After achieving a steady state, O_2_ consumption and CO_2_ production standardized for temperature, barometric pressure, and humidity will be recorded at 1-min intervals for 20–45 min and averaged over the whole measurement period. RMR (kcal/day) and respiratory quotient (CO_2_/O_2_) will then be calculated.

Morningness–Eveningness Questionnaire for Children and Adolescents (MEQ-CA)

Participants will be asked to complete an MEQ-CA which is a 19-item questionnaire to assess habitual waking and bedtimes together with the times of day when they prefer to “perform” [41]. The MEQ-CA score ranges from 16 to 86, with scores below 42 identifying participants as evening types, scores between 42 and 58 as intermediate types, and scores above 58 as morning types.

Pittsburgh sleep quality index (PSQI)

The PSQI will be used to measure sleep quality [42]. It is a 19-item self-report instrument designed to measure sleep quality and disturbance over the previous four weeks. The score range of the questionnaire is 0–21; higher scores (>5) indicate higher levels of sleep disturbances.

Epworth sleepiness scale (ESS)

EES is a short, self-administered questionnaire commonly used to quantify overall excessive daytime sleepiness and evaluate tendency to fall asleep in eight sedentary situations [43]. The total daytime sleepiness score ranges from 0 to 24 (0–7 normal, 8–9 mild excessive, 10–15 moderate excessive, and 16 or above severe excessive).

International physical activity questionnaire, short form (IPAQ-SF)

The short interviewer-administered IPAQ contains seven questions that measure the frequency (days/week) and duration (minutes/day) of vigorous and moderate-intensity activities and walking in bouts of at least 10 min in the last week [44]. Physical activity outcomes from the IPAQ-SF for this study were as follows: weekly minutes spent in vigorous physical activity, moderate-intensity physical activity, walking, and sedentary time.

#### 2.4.2. Outcome Measures

Sleep

The Sleep Profiler-PSG2™ (Advanced Brain Monitoring, Carlsbad, CA, USA) will be used to measure sleep [46]. This minimally invasive device is approved by the Food and Drug Administration (FDA). Its measure is reproducible and validated for gold standard laboratory polysomnography (PSG) in adults and children aged > 6 years. It has three channels: electroencephalography, electro-oculography, and electromyography from frontopolar sites; airflow through a nasal cannula and pressure transducer; head movement and position by actigraphy; snoring with an acoustic microphone; pulse from the forehead and finger; wireless wrist oximetry; and thorax and abdomen effort by respiratory inductive plethysmography. The participants will be equipped by investigators. The records will then be extracted through the Sleep Profiler portal. Validated auto-staging will be applied based on the ratios of the power spectral densities and auto-detection of cortical and microarousals, sleep spindles and ocular activity [47,48]. After data processing, an experimented sleep expert will review the recordings to confirm the accuracy of the auto-sleep staging. The Sleep Profiler-PSG2™ provides total sleep time (TST), sleep onset latency (SOL), wake after sleep onset (WASO), sleep efficiency (SE), number of awakenings lasting more than 30 s, arousal index, and time spent in non-rapid (NREM; Stage-1, Stage-2, and Stage-3) and rapid eye movement (REM) according to American Academy of Sleep Medicine (AASM) recommendations.

Circadian phase and morning cortisol

Five salivary samples will be collected in the participant’s habitual sleep environment in dim light conditions (<20 lux in any direction of gaze) according to the method described by Mandrell et al. (2018) [49]. Participants will allow saliva to collect in their mouth and then drool into a collector tube rather than spitting (Salivette^®^ Sarstedt). Evening saliva samples will be taken for the assessment of dim light melatonin onset (DLMO), a measure of circadian phase. To record the increase in melatonin, participants will be asked to start collecting every hour (3, 2, and 1 h) before bedtime. Saliva will be collected again at bedtime and investigators will wake the participants to take a final sample 1 h after bedtime. The following morning two saliva samples will be taken (on awakening and 1 h after awakening) to measure cortisol peak. The saliva collection tubes will be coded according to the biomarker and collection time (melatonin 3, 2, and 1 h before bedtime, melatonin at bedtime, melatonin 1 h after bedtime, cortisol on awakening, and cortisol 1 h after awakening). After each hourly collection, the tube will be placed in a labeled box in a freezer. The samples will then be stored in a freezer at −80 °C until analysis and treatment by expanded-range enzyme immunoassay.

Energy expenditure and physical activity

Physical activity will be monitored during the intervention using ActiGraph GT3X accelerometers (Pensacola, FL, USA) at a 1-s epoch setting to ensure that participants keep the same level of physical activity between sessions. This multisensory tool continuously collects various motion parameters through a triaxial accelerometer [50]. Sex, age, body weight, and height data will be transferred to estimate the level of physical activity and activity energy expenditure using algorithms developed by the manufacturer’s software (Actilife). Accelerometers will be secured to belts and distributed to the participants on awakening on Day 1. They will be instructed to wear the instruments on their waist until Day 7, and told to remove the accelerometer only when there may be water contact (showering).

Biochemical measures

Venous blood samples will be taken via an indwelling catheter at 07:30 am in the fasting state. Samples will be collected in EDTA K2 Vacutainer^®^ tubes (Becton Dickinson, Franklin Lakes, NJ, USA), Vacutainer^®^ Lithium Heparin tubes (Becton Dickinson, Franklin Lakes, NJ), and in Vacutainer^®^ SST II Advance tubes (Becton Dickinson, Franklin Lakes, NJ, USA). Samples collected will be immediately centrifuged at 3000× *g* for 10 min at 4 °C except for blood samples on SST tubes, which will be centrifuged after 30 min. After centrifugation, the serum aliquots will be frozen and stored at −80 °C until analysis for cytokines; all other blood samples will be analyzed immediately.

Blood samples will be taken at two time points (Days 4 and 7) in each session for the analysis of glucose, cholesterol triglycerides, urea, serum glutamic oxaloacetic transaminase (AST), serum glutamic pyruvic transaminase (ALT), insulin, leptin, ghrelin, adiponectin, GLP-1, PYY-36, nesfatin, irisin, GH, GHRH, TSH, serotonin, kynurenine, CRP, IL-1β, Il-6, TNF-α, IL-4, IL-10, sTNFR1, and sTNFR2. Plasma amino acids will be analyzed. The plasma Trp/LNAAs ratio will be calculated as Trp concentration (in μmol/L) divided by the sum of LNAAs. Changes in all biomarkers will be measured as the differences between Days 4 and 7 of each session.

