Latent factors related to both obesity and/or sleep may affect outcomes of studies investigating the effect of dietary intervention on sleep. For instance, we already showed in previous works that physical activity could affect sleep in adolescents with obesity [64]. Therefore, we underline that these factors should be systematically quantified and added as confounders. Laboratory PSG is considered as the gold standard for sleep assessment. The absence of this measure is perhaps the main limitation of this study. However, gold standard PSG is not a viable option in the context of this research because: (i) it is cumbersome (two measures per session); (ii) differences in sleep quality may result from changes in sleeping environment; and (iii) the protocol already makes strong demands on the adolescent’s personal life during the protocol (three consecutive weeks). The ambulatory wearable device to be used includes all the major aspects of PSG: three EEG channels, airflow, thorax, and abdomen belt and pulse oximetry. Its measurements have been validated and yield results comparable to polysomnography in assessing sleep staging and several other parameters. However, this study is also limited by a small sample size and does not include female subjects. Although it is interesting to look for gender effect, the control of menstrual cycle phase in adolescent girls would be complicated and incompatible with such a study design. Previous studies have shown that menstrual cycle phase impacts sleep, circadian rhythm, and food intake, which could lead to biased assessments [65]. Finally, the effect of such an intervention in the medium and long term remains to be determined and would be interesting. Motivating the adolescents to follow this study protocol for a longer period is challenging and may severely penalize the feasibility of the study. However, previous studies already showed that dietary manipulation affect sleep significantly even over a shorter period of time than that of this study [66,67].

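### Every night behind the primary sleep-efficiency contrast includes a forced waking 1 h after bedtime, which adds imposed wake and noise to the outcome without by itself biasing the protein comparison

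*Protocol article*

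**What the plan says.** The Abstract sets the endpoint: "The primary outcome is sleep efficiency measured through in-home electroencephalogram recordings". Section 2.3.2 (Experimental Sessions) gives the schedule. On Night 3, "five saliva samples will be collected to capture DLMO (3, 2, and 1 h before bedtime, bedtime, and 1 h after bedtime", and for the same night "Participants will be fitted with the Sleep Profiler-PSG2 TM for the night". The second measurement repeats this: "Similar to Night 3, participants will collect five saliva samples and undergo electroencephalogram (EEG) recordings during Night 6". Section 2.4.2 (Outcome Measures, circadian phase and morning cortisol) explains how the last sample is obtained: "investigators will wake the participants to take a final sample 1 h after bedtime".

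Section 2.4.2 (Sleep) describes auto-staging, expert review to confirm the staging, and a list of indices supplied by the device, among them sleep efficiency, SOL, WASO, awakenings and arousal index. The Discussion counts the sleep recordings when it explains why laboratory polysomnography was rejected: "it is cumbersome (two measures per session". Section 2.6.1 bases the sample size on the pre/post difference in sleep efficiency compared between the three sessions.

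**The concern.** A procedure for a secondary outcome (melatonin onset) acts directly on the primary outcome. Rousing an adolescent, collecting saliva and letting him settle again creates wake during the sleep period. Correctly staged, that is wake, and it enters sleep efficiency, WASO, the number of awakenings and the arousal index. It interrupts the early part of the night, so it touches sleep staging. In anyone not yet asleep at 1 h, it disturbs sleep onset latency as well.

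Three things are at stake:

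- absolute values of sleep efficiency and WASO will not describe undisturbed sleep;
- night-to-night variation in the length of the interruption goes into the within-subject error that the crossover design is meant to keep small;
- the outcome becomes a mixture of spontaneous sleep efficiency and recovery from a forced waking, which is a different quantity from the one named.

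The Discussion presents the method as minimally intrusive and justifies the habitual sleeping environment by the wish to avoid bias in sleep assessment. It does not list the waking among the limitations.

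**Working it through.** **Step 1: match the two schedules.**

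| Night of session | Saliva series with waking at 1 h | Sleep recording |
|---|---|---|
| 3 (end of washout) | yes | yes |
| 6 (end of supplementation) | yes | yes |

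Two recordings per session × 3 sessions = 6 nights, all interrupted. The only other use of the sleep recorder described is familiarisation before the sessions (section 2.3.2). There is no undisturbed recorded night in the contrast.

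**Step 2: reproduce the planned sample size.** Inputs from section 2.6.1: alpha 0.017, power 90%, correlation 0.5, effect size 0.8; two-sided testing from section 2.6.2.

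n = (z(0.9915) + z(0.90))² × 2(1 − 0.5) / 0.8² = (2.387 + 1.282)² × 1 / 0.64 = 13.456 / 0.64 = 21.03, rounded up to 22.

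The stated 22 reproduces by the normal approximation, so no stated figure is wrong. With the exact paired t test, power is 0.866 at n = 22 and 0.901 at n = 24. The exact values are used below.

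**Step 3: level shift.** Loss in sleep efficiency = 100 × imposed wake / time in bed. The article gives neither the length of the waking nor the time in bed, so both are assumed.

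| Time in bed | 10 min | 20 min | 30 min |
|---|---|---|---|
| 420 min | 2.4 | 4.8 | 7.1 |
| 480 min | 2.1 | 4.2 | 6.3 |
| 540 min | 1.9 | 3.7 | 5.6 |

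These are percentage points of absolute sleep efficiency on a single night. A loss that is constant over nights cancels in the pre/post difference and between sessions.

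**Step 4: noise.** Only variation in the imposed wake survives the contrast. Assumptions: SD of sleep efficiency 5 points on a single night, 480 min in bed, the stated 0.5 read as the night-to-night correlation, added wake unrelated to the rest of the night, and a planned effect of 0.8 that does not already include this noise.

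Within-person variance per night = (1 − 0.5) × 5² = 12.5. An imposed-wake SD of s minutes is w = 100 × s / 480 points. Let r be the within-person correlation of the imposed wake between nights:

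inflation = (12.5 + (1 − r) × w²) / 12.5, and the standardised effect becomes 0.8 / √inflation.

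| s (min) | w² | Inflation, r = 0 | Power, n = 22 | Inflation, r = 0.5 | Power, n = 22 |
|---|---|---|---|---|---|
| 5 | 1.085 | 1.09 | 0.83 | 1.04 | 0.85 |
| 8 | 2.778 | 1.22 | 0.78 | 1.11 | 0.82 |
| 10 | 4.340 | 1.35 | 0.73 | 1.17 | 0.80 |

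The reference without added noise is 0.87. If all 24 complete, the reference is 0.90 and the same formula gives 0.87 to 0.78 (r = 0) or 0.89 to 0.84 (r = 0.5).

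**The case against.** The strongest reply is that the waking is common to all three proteins and to both time points, in a blinded trial in which each participant is his own control. A constant loss therefore cancels. This stands. A reader might infer from the schedule that the protein comparison is biased; the documents do not support that. Nor is it fair to set the 2-6 point level shift beside a target of 0.8 × 5 = 4 points, because the first mostly cancels and the second is a difference between conditions.

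A reader might also argue that return to sleep depends on the protein and so creates a differential artefact. Nothing in the article shows this. If it were true, faster return to sleep could be part of the effect sought. That bears on the remedy: deleting return-to-sleep time from the primary definition could discard real effect.

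The power figures rest on values that are not in the article, and stable personal differences in resettling would cancel too, which is why a range is given.

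It can also be said that epoch handling belongs in a scoring manual or analysis plan that is not shown. That is fair for the handling rule, and no fault is found with its absence. The point concerns a procedure the article does state. A later rule could remove the imposed minutes, but it could not restore the interrupted early sleep.

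Finally, the late sample serves a stated secondary objective. The Introduction notes that sleep timing is delayed in adolescence, so ending the series at bedtime could miss late onsets. This stands as a reason to be careful about how the sample is moved.

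**Conclusion.** The point holds as a matter of measurement quality. All six nights behind the primary contrast contain investigator-imposed wake, which as described counts in sleep efficiency, WASO, awakenings and arousal index, affects early-night staging, and affects SOL in anyone not yet asleep at 1 h. The consequences are lower absolute sleep efficiency, added within-subject noise, and an outcome that partly measures recovery from being woken. Bias in the randomised comparison is not shown.

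The size cannot be computed from the article, which gives no time in bed, SD of sleep efficiency or duration of the waking. Under the assumptions above, power at n = 22 falls from 0.87 to between 0.85 and 0.73, depending on how variable the imposed wake is and how far it is correlated within person. The lower end should not be read as the trial's actual power: it needs a 10 min SD and no within-person correlation.

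**What to change.** **Option 1, keep the schedule.** Log the clock time of each waking and of sample completion (lights out). Remove only that investigator-imposed interval, from both wake time and time in bed, when deriving sleep efficiency, WASO, awakenings and arousal index on Nights 3 and 6. Keep the later return-to-sleep time in the primary definition, because it may depend on treatment. Report two sensitivity analyses: one with nothing removed, and one that also masks return to sleep. The cost is two logged times per night and one scoring rule. This does not repair early-night staging, which should be listed as a limitation.

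**Option 2, separate the procedures.** Take the evening saliva series on Nights 2 and 5, which are not recorded. This also protects staging and SOL on the recorded nights. It needs a small amendment but no extra samples. The cost falls on melatonin onset, a secondary outcome: it would be measured one shake day earlier, and no longer on the same night as the EEG and just before the next-morning saliva and blood samples. The waking would fall on the night before each recorded one, still alike in all conditions.

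Under either option, the article should name the waking where it discusses intrusiveness and limitations.
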